Reasons for discontinuation are the following: (1) withdrawal of informed consent, (2) participants from the CG (without EME) starting in an OT-EME group during the data collection phase and (3) participants of the EG (with EME) missing more than three of the eight EME lessons. All data collected until withdrawal will be used in the analysis. If a participant decides to withdraw from the follow-up, the reasons for the withdrawal will be recorded for the subsequent analysis respectively the interpretation of the results. We will make all attempts to closely follow up participants and therefore minimise missingness throughout data collection. At each time point, participants of both groups will be invited to fill in the questionnaires via Redcap by presenting or e-mailing the correct web link and, if necessary, up to two reminders after 4–5 days each. No reaction will lead to a reminder for contacting the principal investigator, if they need any support to continue with the study, with a clear statement, that they are not obliged to answer this reminder or justify their drop-out if they do not want to.

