#### Statistical analysis

We will emulate a prospective interventional study that makes causal inferences on the effectiveness of adding EME to the standard care using a target trial emulation approach (see table 4).^28 29^

**Table 4 T4:** Target trial protocol components

Protocol component	Emulated target trial
Eligibility criteria	Inclusion criteria: Living in Switzerland Age ≥18 years Diagnosed with post-COVID-19 condition Confirmed experience of living with fatigue (MFIS, cut-off >38)^47^ No major depression (Beck depression inventory (BDI)-FS cut-off <8)^48^ No major cognitive impairments (Mini-Mental State Examination (MMSE) cut-off of ≥26 for the experimental group and MMSE-telephone version for the control group (CG), cut-off≥21)^49 50^ Ability to understand and speak German, French or Italian and to fulfil the assessments Ability to give informed consent as documented by signature Exclusion criteria: Participation in an energy management education (EME) group or starting it during the study duration (only CG) History of severe neurological diseases (eg, stroke, MS and Morbus Parkinson’s disease) or mental health disorders (eg, schizophrenia, major depression, schizophrenia or dementia) Inability to follow the procedures of the study, for example, due to language problems, psychological disorders, dementia, etc.
Recruitment	Experimental group (eg,) participants at three study sites (INSEL, USZ, REHB) consecutive ongoing from mid-July 2024 up to the required number of 61 participants; maximum until end of 2025 A register for potential CG participants disseminated through the national patient organisations and specified healthcare providers
Follow-up	24 weeks after enrolment in the study

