Descriptive statistics will be used for all outcome measures at each measurement time to summarise results. To ensure that PS matching adequately balances measured confounders, we will carefully assess and report standardised differences between treatment groups before and after matching.^40^ Standardised differences are widely used because they are unaffected by sample size and provide a consistent measure of imbalance. A standardised difference of less than 10% (0.1 in absolute value) will be considered indicative of a clinically relevant balance between groups. Variables with standardised differences of greater than 10% will be flagged for potential residual confounding and addressed in sensitivity analyses.

Our causal contrast of interest will be the per-protocol effect, so to analyse the effect of adding EME to the standard care on the dependent continuous variables for both primary and secondary outcomes, an adjusted repeated measures mixed-effects linear regression model will be used. In addition to the covariates already included in the matching phase, we are aiming to include additional potential covariates related to the clinical history of long-COVID (eg, fatigue intensity, fatigue impact) and socio-demographic data (eg, education, occupation status).

Using PS matching combined with regression methods is a robust approach to account for measured confounding. However, this approach does not address unmeasured confounding, which could bias the results. To acknowledge this limitation and mitigate its impact, we will perform a sensitivity analysis to evaluate the robustness of your findings to potential unmeasured confounding. We will perform a simulated bias analysis to estimate the potential impact of unmeasured confounding. We will specify plausible distributions for an unmeasured confounder and assess its potential effect on the treatment-outcome relationship.^41^ In addition, we plan to conduct an E-value analysis for assessing whether our results are likely robust even in the presence of unmeasured confounders.^42^ The E-value quantifies the minimum strength of association that an unmeasured confounder would need to have with both the treatment and the outcome (beyond measured confounders) to explain away the observed treatment effect.^43^

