#### Selection bias

This common flaw of observational studies, we address by not using any information collected in the EG after the baseline period to determine which individuals from the register should be enrolled in the CG. By defining the recruitment of controls in two stages and having clear eligibility criteria, we create a structured approach to estimate causal effects even in the absence of true randomisation, based on an unbiased sample.

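### Discontinuing participants for missed lessons or for starting EME, with adjustment described at baseline only, leaves the per-protocol comparison at T2 open to selection bias of uncertain direction

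*Protocol article*

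**What the plan says.** The Statistical analysis section names the target: "Our causal contrast of interest will be the per-protocol effect". Table 4 repeats it.

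The Data collection section gives three reasons for discontinuation. Besides withdrawal of consent, they are "participants from the CG (without EME) starting in an OT-EME group during the data collection phase" and "participants of the EG (with EME) missing more than three of the eight EME lessons". It then states: "All data collected until withdrawal will be used in the analysis".

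Table 4 lists among its exclusion criteria: "Participation in an energy management education (EME) group or starting it during the study duration (only CG").

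Matching uses sex, age and clinical history at baseline. The outcome model is a covariate-adjusted linear mixed model for repeated measures. Its further covariates are clinical-history and sociodemographic variables, none of them named as measured after baseline. The Missing data section makes complete case the default, with multiple imputation as a robustness check. The Selection bias section describes how controls are chosen from the register and concludes that effects are estimated "based on an unbiased sample".

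**The concern.** Attendance and starting EME are events after time zero, and health at that moment can influence both. In people with severe fatigue, those doing worse may be the ones who miss face-to-face sessions. If they drop out of the T2 comparison, the remaining experimental participants look better than the whole group would have looked under full attendance. Controls leave by a different rule, so the two selections need not cancel. Matching and adjustment at baseline do not remove selection that operates through later health.

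T2 is the main assessment. If questionnaires stop at deviation, a complete as-started comparison at T2 cannot be made, and no analysis plan can restore outcomes that were never collected.

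The Table 4 wording adds a second problem. Whether a control will start EME during the study cannot be known when eligibility is checked, yet a target trial emulation needs eligibility that can be assessed at time zero.

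**Working it through.** **1. The plan's own figure.** Inputs from the Sample size section: difference 1.5, SD 2.2, power 90%, alpha 0.05 (two-sided assumed), 24% at T2.

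n per arm = 2 × [2.2 × (1.960 + 1.282) / 1.5]² = 45.2, rounded up to 46. Then 46 / (1 − 0.24) = 60.5, rounded up to 61 per arm, 122 in total. This matches. The protocol calls the 24% a follow-up rate, but it reproduces 122 only as a loss rate.

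**2. When discontinuation would fall.** Lessons 1 to 7 are weekly, T1 follows lesson 7 (week 6), and lesson 8 comes about 8 weeks later, near T2 (week 14). A fourth missed lesson can therefore occur at lessons 4 to 6 (before T1), at lesson 7 (at T1) or at lesson 8 (about T2). Some of those discontinued would contribute T0 only.

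**3. Size of the bias, experimental group.** Let f be the share discontinued. Let d be how much worse those people would have scored at T2 under full attendance than those retained. Bias = f × d. Neither f nor d is in the documents, so both are assumed. The upper value of f is the plan's own 24% loss allowance, and d = 1.1 is 0.5 × 2.2. With 46 per arm analysed, SE = 2.2 × √(2/46) = 0.459, and the type I error is P(|Z + bias/SE| > 1.96).

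| f | Bias (points) | Share of 1.5 | Type I error |
|---|---|---|---|
| 5% | +0.055 | 3.7% | 0.052 |
| 10% | +0.110 | 7.3% | 0.057 |
| 15% | +0.165 | 11.0% | 0.065 |
| 24% | +0.264 | 17.6% | 0.089 |

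With d = −1.1 (better-doing people stop) every bias changes sign. With d = 2.2, a full SD, the range is +0.11 to +0.53.

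**4. Control group.** Let g be the share starting EME and dc how much worse they are than other controls. Bias = −g × dc. At g = 10% this is −0.11 if starters are worse by 1.1 points and +0.11 if they are better by 1.1.

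**5. Does keeping earlier data help?** A large simulation (400,000 per arm, true effect 1.5, SD 2.2) let post-baseline health drive both discontinuation and T2. It compared complete case with a likelihood-type analysis using T0 and T1.

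| Scenario | Complete case | Using T1 |
|---|---|---|
| EG 15%, worse stop | +0.17 | +0.12 |
| Same, T1 not collected | +0.17 | +0.17 |
| EG 24%, worse stop | +0.27 | +0.18 |
| EG 15%, better stop | −0.18 | −0.12 |
| EG 15%, at random | about 0 | about 0 |
| CG 10%, worse start EME | −0.12 | −0.09 |
| CG 10%, better start EME | +0.12 | +0.09 |
| Worse leave both arms, EG 15% and CG 10% | +0.05 | +0.04 |
| Worse leave both arms, 15% each | about 0 | about 0 |

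T1 data remove about 30% of the bias (1 − 0.122/0.173), and nothing if T1 is missing.

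**6. Table 4 against the rest.** Table 2 places the control eligibility check at week −2. The Eligibility criteria section excludes only previous participation in an EME group. Data collection treats a control's later start as discontinuation, with earlier data kept. Table 4 treats the same event as exclusion. Whether such a control is removed or censored is therefore undefined.

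**The case against.** Much can be said for the plan. A per-protocol contrast is legitimate and openly declared. Discontinued people are censored, not deleted. The mixed model can use T0 and T1, and multiple imputation is planned as a check. The article is condensed, so adherence weighting or an as-started analysis may stand in a fuller plan. Their absence here is weak evidence and is not the point. The sensitivity analyses for unmeasured confounding are also sound, although they address the link between treatment and outcome, not selection after baseline.

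Several stronger readings are tempting, and the documents do not support them:

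- That the effect is biased upward. The protocol does not say who misses lessons, who starts EME or how many. Both signs are possible.
- That the loss is one-sided. Controls have a discontinuation rule too, and similar selection in both arms can cancel.
- That the comparison becomes EME completers against people who never sought EME. Participants missing up to three lessons remain in, and controls leave for starting a group, not for seeking one.
- That data collection certainly stops. The section does not say so outright, and it promises close follow-up and minimal missingness. That it stops is the natural reading of discontinuation listed alongside withdrawal of consent, but it needs to be stated either way.
- That the Selection bias section claims protection against later selection. Its argument concerns the choice of controls at enrolment. It simply does not reach post-baseline events.

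What stands is the pairing of post-baseline discontinuation with adjustment described at baseline, the unclear follow-up after deviation, and the Table 4 conflict.

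**Conclusion.** The point holds as a risk of selection bias of uncertain direction, plausibly in favour of EME. On the assumption that 5% to 24% of the experimental group are discontinued and would have scored 0.5 SD worse, the bias in self-efficacy at T2 is about +0.06 to +0.26 points. That is 4% to 18% of the 1.5-point target and well below the 0.92 minimal clinically important difference. The sign reverses under the opposite assumption, and discontinued controls can offset or add to it. The range is illustrative because none of its inputs apart from the SD and the 24% allowance comes from the protocol. No size can be given for the fatigue impact scale, for which the article states no SD.

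The bias alone would not overturn a true effect of the planned size. It deserves correction because missing outcomes cannot be recovered later and the remedy is cheap. The Table 4 conflict needs no assumption.

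**What to change.** 1. In Data collection, state that only withdrawal of consent ends data collection. Record missed lessons or starting EME as deviations, with dates, and keep sending the T1 to T3 questionnaires.
2. Report the as-started effect at T2 in all matched participants beside the per-protocol effect.
3. Delete the future event from the exclusion criteria in Table 4, so that it agrees with the Eligibility criteria and Data collection sections.

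Optionally, add a sensitivity analysis with inverse-probability-of-censoring weights on a small set of predictors, if deviations are numerous enough. With 10% to 20% of 61 deviating there would be only about 6 to 12 events, and T1 scores cannot predict deviations before week 6. This is why it should not be the main remedy.

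The cost is a minor amendment, a few more reminders (the questionnaires are already online) and one additional reported estimate, which may be smaller than the per-protocol one. It is best done soon: the Project status section expects data collection to run until about the end of 2025.

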### Objectives

The primary aim is to compare the effectiveness of the standard care for persons with long COVID-related fatigue plus participating in an EME group (revised edition 2023), with the standard care without EME at post-intervention (T2; week 14).

The secondary aim is to assess the energy management behavioural strategies applied in daily routines in persons living with long COVID, their feasibility and the factors influencing behavioural changes (T3, week 24).

The third aim is to evaluate the cost-effectiveness profile of the intervention by performing an economic evaluation alongside the trial.

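### Ending follow-up for EME participants who miss more than three lessons selects the experimental arm on a post-baseline event that the stated per-protocol analysis does not handle; the T2 contrast is likely, not certain, to favour EME

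*Protocol article*

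**What the plan says.** The Data collection section gives three reasons for discontinuation. Besides withdrawal of consent there is one rule for each arm. For controls it is "participants from the CG (without EME) starting in an OT-EME group during the data collection phase". For the EG it is "participants of the EG (with EME) missing more than three of the eight EME lessons". The section then states: "All data collected until withdrawal will be used in the analysis". Nowhere does it say that a participant discontinued for low attendance goes on completing questionnaires.

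The Statistical analysis section states: "Our causal contrast of interest will be the per-protocol effect". Table 4 names the same contrast and no other. For estimation, "an adjusted repeated measures mixed-effects linear regression model will be used". The adjustment set is the matching variables plus further baseline clinical-history and sociodemographic covariates, with fatigue intensity and impact among the examples. The Missing data section makes complete-case analysis the default and multiple imputation a robustness check. The abstract places the main assessment at T2, week 14.

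**The concern.** Missing lessons happens after baseline. Most lessons are face-to-face groups, and the Introduction describes fatigue and post-exertional malaise as leading symptoms that limit daily and social activity. People whose illness worsens, or who have little confidence in the strategies, can be expected to miss more sessions. Confidence in the strategies is what the self-efficacy outcome (SEPECSA) measures.

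If these people leave follow-up, the T2 mean in the EG describes those who attended at least five of eight lessons, while the control mean has no corresponding restriction. Matching and baseline covariates balance the arms at T0. They do not restore balance after one arm has been thinned by what happened between T0 and the fourth missed lesson. The simulated bias analysis and the E-value address an unmeasured confounder in general, not this selection.

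At stake is the T2 contrast and also the economic evaluation, which could lose people who used EME places and gained little. A later analysis plan can choose another model, but it cannot recover T2 questionnaires that were never sent.

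**Working it through.** **1. The plan's own figure.** Inputs from Sample size: difference 1.5, SD 2.2, power 90%, alpha 0.05 (two-sided reproduces the total), 24% at T2.
- n per arm = 2 × [2.2 × (1.960 + 1.282) / 1.5]² = 45.2, rounded up to 46.
- 46 / (1 − 0.24) = 60.5, rounded up to 61 per arm, total 122.

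This matches the protocol. The 24% works only as a loss, although it is worded as a follow-up rate. The sample size is not in dispute; 46 per arm is carried forward.

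**2. When the rule can take effect.** Lessons 1 to 7 are weekly from week 0, and lesson 8 comes about 8 weeks after lesson 7. The fourth missed lesson can therefore fall at lessons 4 to 7 (weeks 3 to 6, before or at T1) or at lesson 8 (about week 14, when T2 is due). Anyone with four misses among the first seven lessons crosses the threshold well before T2, and some do so before T1.

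**3. Bias if low attenders leave the analysis entirely.** The documents give neither the share q of the EG that crosses the threshold nor the correlation r between attendance propensity and T2 SEPECSA. Both are assumed. With no true effect and the lowest q of a normal attendance propensity removed from the EG only:

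bias = r × 2.2 × φ(z_q) / (1 − q)

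The SE of the T2 difference is 2.2 × √(2/46) = 0.459, and the two-sided rejection rate is P(Z > 1.96 − bias/SE) + P(Z < −1.96 − bias/SE).

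| q | r | φ(z_q)/(1−q) | Bias (points) | Share of 1.5 | Rejection rate under the null |
|---|---|---|---|---|---|
| 5% | 0.3 | 0.109 | 0.07 | 5% | 5.3% |
| 5% | 0.5 | 0.109 | 0.12 | 8% | 5.8% |
| 10% | 0.3 | 0.195 | 0.13 | 9% | 5.9% |
| 10% | 0.5 | 0.195 | 0.21 | 14% | 7.5% |
| 20% | 0.3 | 0.350 | 0.23 | 15% | 8.0% |
| 20% | 0.5 | 0.350 | 0.385 | 26% | 13.4% |

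Of 61 EG participants, 10% to 20% is about 6 to 12 people.

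**4. Bias if their early data enter the mixed model.** Assume a between-visit correlation ρ and an attendance propensity equally correlated with the score at each visit. Let λ = φ(z_q)/(1 − q) and δ = λ(λ − z_q). The correlation among those retained is b = (ρ − r²δ)/(1 − r²δ). The remaining bias is (1 − b) of the value in step 3 when T0 alone is used, and (1 − b)/(1 + b) of it when T0 and T1 are used.
- q = 10%, r = 0.3, ρ = 0.6: δ = 0.195 × (0.195 + 1.282) = 0.288 and b = 0.589. Remaining bias: 0.05 with T0 only, 0.03 with T0 and T1.
- q = 20%, r = 0.5, ρ = 0.6: δ = 0.350 × (0.350 + 0.842) = 0.417 and b = 0.553. Remaining bias: 0.17 with T0 only, 0.11 with T0 and T1.

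More remains when attendance tracks later deterioration more closely than it tracks T0 and T1. Simulation at q = 20%, r = 0.3 to 0.5 and ρ = 0.5 to 0.7 leaves 0.04 to 0.24 points with T0 and T1 used for everyone. Together these give roughly 0.03 to 0.24 points. If T1 is also lost, the T0-only values apply; at ρ = 0.4 they reach 0.26.

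**The case against.** The strongest defence is that a per-protocol contrast needs a definition of deviation in each arm, and the protocol gives one: too few lessons in the EG, starting EME among controls. Open-ended standard care has no attendance schedule to enforce. Data up to withdrawal are kept, a repeated-measures model can use them, fatigue covariates are planned, and multiple imputation is a robustness check. The section also promises close follow-up and invitations at each time point for both groups. Much of this stands. It is why the figures in step 3 are an upper case within the assumed ranges, and why the per-protocol contrast is not itself a fault. It does not remove the point: low attendance is listed as a discontinuation reason, no continued follow-up of these people is stated, and a complete-case default could discard the early data that would help.

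A reader might infer more than the text supports:
- *That bias towards EME is established.* The documents contain no attendance or outcome data. People who recover may also stop attending, and a negative correlation would reverse the sign.
- *That controls are unselected and face no rule.* They have the crossover rule and are self-registered volunteers, as the Volunteer bias section acknowledges. Only an engagement rule is absent.
- *That the matched controls of discontinued participants stay in.* The handling of broken pairs is not described.
- *That every low attender lacks T2.* The word withdrawal could mean consent only, and someone who crosses the threshold at lesson 8 may still answer T2.
- *That the Selection bias section contradicts the rule.* Its assurance of "not using any information collected in the EG after the baseline period" concerns which register members are chosen as controls. It does not cover who leaves the EG, so it is incomplete on this point but not contradicted.

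**Conclusion.** The point holds in limited form. An EG-only, post-baseline and plausibly prognostic event appears to end follow-up, and no stated method deals with the resulting selection. The T2 contrast is likely to favour EME. For SEPECSA the null bias is about 0.13 to 0.39 points if low attenders drop out of the analysis entirely, and roughly 0.03 to 0.24 points if their T0 and T1 data are used. These ranges assume that 10% to 20% are removed, a correlation of 0.3 to 0.5 with T2, SD 2.2, and the between-visit correlations above. If only 5% cross the threshold, even complete removal gives 0.07 to 0.12 points. The largest value, 0.385, is 42% of the 0.92 minimal clinically important difference. Nothing was computed for the fatigue impact scale.

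A reader might conclude that the result would be unusable, or that the per-protocol contrast must give way as the main estimate. Neither follows: the bias is moderate at most under these assumptions, and which contrast leads is an estimand choice on which statisticians may differ. This is something the plan should fix, not a fatal flaw.

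**What to change.** 1. Amend the discontinuation list in Data collection so that missing more than three lessons is recorded as a protocol deviation but does not end follow-up. Keep inviting every consenting EG participant to the T1, T2, T3 and cost questionnaires.
2. Alongside the per-protocol effect, report the T2 estimate and the cost-effectiveness result for all EG participants who started EME against their matched controls, regardless of attendance.
3. In the per-protocol estimate, account for attendance-related censoring with the T0 and T1 outcomes already collected, for example by inverse-probability-of-censoring weights.

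The cost is a short amendment and a few extra online questionnaires sent through the existing invitation and reminder system. The as-started estimate may be smaller than the per-protocol one. The first change is the urgent one, because it helps only participants whose follow-up is still open.
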